### Description of the interventions

#### Control group

Women in the control group will receive standard medical care during pregnancy and postpartum as dictated by their obstetricians. Any advice regarding infant nutrition or treatment of inverted nipples will be left to the primary physician, including possible use of the syringe technique, in which case the participant will continue in the study and will be analyzed in her group as dictated by the intention to treat principle. We will provide the participants in the control group with documentation on breastfeeding-associated complications, use of artificial devices to correct the inverted nipple, such as nipple shields, Niplette, inverted syringe, or breast pump, and the number of artificial milk feeds given to the newborn with their justification in a diary. The research assistant will send weekly reminders to the participants in the control group using e-mail, telephone messages, or communication through social media, to remind them about documentation in the diary.

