### Data collection

At baseline, we will collect information on socio-demographics such as maternal age, parity, education, employment, family monthly income, previous breastfeeding, and longest duration of previous breastfeeding if present. Data on gestational age, mode of delivery, newborn’s gender, birth weight, APGAR score, and nursery admission status (regular vs intensive care), as well as grading of maternal nipple inversion will be recorded.

On the first day postpartum, the following information will be collected: exclusive breastfeeding (yes/no), use of artificial milk (number of feeds in 24 h, justification), sore nipple (yes/no), pain while breastfeeding (yes/no), compliance with the use of the syringe technique before each breastfeed (experimental group only), and the use of other conservative methods to pull out the nipple (in both groups).

On the third and seventh days postpartum, we will call the participants to remind them about documentation in the diary, collect data about maternal breastfeeding evaluation (day 7 only), and address any questions.

The diary will be collected at 30 and 40 days during the participant’s postpartum visit to her obstetrician. We will also administer the Postpartum Quality of Life instrument, and collect data on the infant’s weight at month 1 from the infant’s health record. The eversion of the nipple will also be assessed by the research assistant during this visit.

On months 3 and 6 postpartum, we will call the participants to collect information on infant feeding methods, adverse events, and infants’ weight at 3 and 6 months.

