### Sample size

Based on data from a previous breastfeeding clinical trial that we conducted, 45% of women continue to breastfeed exclusively for 1 month postpartum [21]. We hypothesize that in women with inverted nipples, 40% of the experimental group and 5% of the control group will be exclusively breastfeeding at 1 month. To have 90% power and 5% type I error, and using the online calculator available at http://powerandsamplesize.com/Calculators/Compare-2-Proportions/2-Sample-Equality, we will need 25 women in each group to detect this 35% difference in the exclusive breastfeeding rates between the two groups.

In our recent breastfeeding support trial [21], the attrition rate was 40%. Since women with inverted nipples face more difficulties in breastfeeding than women with normally everted nipples, we hypothesize that 50% attrition rate would be a reasonable assumption for the proposed study. To account for a potential attrition rate of 50%, we inflated the sample size to become 100 women in total.

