### Statistical methods

We will compare continuous variables using Student’s *t* test and categorical variables using Chi square test. Non-parametric tests will be used to analyze variables with skewed distribution or when the number of analyzed subjects is less than 30. We will calculate the crude rates of exclusive breastfeeding and mixed feeding at 1, 3, and 6 months in both groups. The 95% confidence intervals for the crude rates of breastfeeding will be computed using the normal approximation to the binomial distribution. We will also conduct multivariable logistic regression analysis to investigate the association between exclusive breastfeeding at 1 month (dependent variable) and the use of the inverted syringe (predictor) adjusting for potential confounders such as the grade of inverted nipple. Missing data will be imputed using last observation carried forward for the breastfeeding outcomes at 1, 3, and 6 months if breastfeeding was discontinued on last follow-up, the average value for continuous variables, and random replacement to maintain proportions for categorical variables, as appropriate. We will conduct sensitivity analysis with and without the imputed missing data to assess the impact of missing data on the primary outcome. We will also conduct repeated measurement analyses using generalized estimating equations (GEE) to explore the effect of the intervention over time. Blinded, intention to treat analysis will be conducted using the Statistical Package for Social Sciences (SPSS) version 24. A *p* value of < 0.05 will indicate statistical significance.

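### For women lost before the 1-month visit with their diary unrecovered, the text lists no feeding observation after day 1, so carry-forward will rarely apply to those who stopped in between

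*Protocol article*

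**What the plan says.** Four parts of the protocol article bear on this.

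- **Feeding data by contact (Data collection).** Feeding is asked directly on day 1: "On the first day postpartum, the following information will be collected: exclusive breastfeeding (yes/no), use of artificial milk". It is asked again by telephone at months 3 and 6. The calls on days 3 and 7 are described as serving to "remind them about documentation in the diary, collect data about maternal breastfeeding evaluation (day 7 only), and address any questions".
- **The diary (Control group, Intervention group, Data collection).** In both arms the mother records "the number of artificial milk feeds given to the newborn with their justification in a diary". Weekly contacts are described as reminders; in the control arm they are "to remind them about documentation in the diary". The diary reaches the trial late: "The diary will be collected at 30 and 40 days during the participant’s postpartum visit to her obstetrician".
- **Imputation (Statistical methods).** The rule for feeding outcomes is "last observation carried forward for the breastfeeding outcomes at 1, 3, and 6 months if breastfeeding was discontinued on last follow-up". Missing categorical values are otherwise replaced at random so that proportions are preserved, where appropriate. The primary outcome is also to be examined with and without imputed data.
- **Attrition (Sample size).** The earlier trial lost 40%. Because women with inverted nipples have more difficulty breastfeeding, "we hypothesize that 50% attrition rate would be a reasonable assumption for the proposed study".

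**The concern.** The carry-forward rule has a sensible purpose: a woman known to have stopped breastfeeding before she was lost should count as not exclusively breastfeeding at 1 month. To do that, the trial must hold a record that she stopped. For the 3- and 6-month outcomes, the 1-month visit or the 3-month call can supply it. For the 1-month outcome, the only feeding record listed before the visit, apart from the diary, is day 1, which is also the day on which allocation is revealed. Women are enrolled only if they intend to breastfeed, so few should have stopped by then. A negative answer on exclusivity that day may also mean mixed feeding and not discontinuation.

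The women affected are unlikely to be a random subset. The protocol itself ties its higher attrition assumption to breastfeeding difficulty, so stopping early and being lost may well go together. If such a woman is filled at random from the observed proportions, she can enter the primary analysis as exclusively breastfeeding.

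**Working it through.** **1. The plan's own sample size.** Inputs from Sample size: 40% against 5%, power 90%, type I error 5%. Taken as two-sided with unpooled variance:

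n = (0.40 × 0.60 + 0.05 × 0.95) × ((1.960 + 1.282) / 0.35)² = 24.66, rounded up to 25 per group.

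With 50% attrition, 25 / (1 − 0.5) = 50 per group, or 100 in total. Both figures reproduce, and nothing here disputes them.

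**2. Following one woman through the text.** Suppose she stops on day 4 and does not attend the 1-month visit.

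| Contact | Feeding information listed | Available for her? |
|---|---|---|
| Day 1 | Exclusivity and artificial feeds | Yes, but she had not stopped |
| Days 3 and 7 | None listed | No |
| Weekly contacts | Reminders only | No |
| Diary | Artificial feeds | Only if recovered |
| 1-month visit | Diary handed in | Missed |

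If the diary is not recovered, her last listed feeding observation is day 1, and the condition for carrying forward is not met.

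**3. How many women could be affected.** With 50 per arm and a proportion d lost before the 1-month visit, 50 × d lack the outcome:

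- d = 30%: 15 per arm
- d = 40%: 20 per arm
- d = 50%: 25 per arm

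These are upper limits. They place all attrition before month 1, and some of these women may have a recovered diary or have stopped by day 1.

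**4. What the added questions could recover.** Let s be the share of these women who stopped after day 1, report it on the day-3 or day-7 call, and never return a diary. The documents give no value for s, so 25%, 50% and 75% are assumptions. The number turned from unknown to known non-exclusive per arm is 50 × d × s:

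| d | s = 25% | s = 50% | s = 75% |
|---|---|---|---|
| 30% | 3.75 | 7.5 | 11.25 |
| 40% | 5 | 10 | 15 |
| 50% | 6.25 | 12.5 | 18.75 |

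**5. Why the route of imputation matters.** Assume the women observed at 1 month show the planning rates of 40% and 5%, with the same loss d in each arm.

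- (a) Every missing woman counted as stopped: rates (1 − d) × 40% and (1 − d) × 5%. At d = 50% this is 20% against 2.5%, a difference of 17.5 points.
- (b) Random replacement within arm: rates stay at 40% and 5%, a difference of 35 points.
- (c) Random replacement from the pooled rate, (40% + 5%) / 2 = 22.5%: at d = 50%, 0.5 × 40% + 0.5 × 22.5% = 31.25% against 0.5 × 5% + 0.5 × 22.5% = 13.75%, a difference of 17.5 points.

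Under (a) and (c) the difference is (1 − d) × 35 points: 24.5 at d = 30%, 21 at 40% and 17.5 at 50%. Under (b) it is always 35. Leaving the women out also gives 35, on fewer women. Scenario (a) is an extreme, since not every lost woman will have stopped, but it shows that the route applied can change the estimate by up to a factor of two.

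**The case against.** The strongest reply is that the list of contacts may not be complete. The secondary outcomes include complications at 1 week, which the day-7 call does not list either. The 1-month visit names no direct feeding question, although it is the primary time point. The assessment schedule is in Fig. 1, which was not available for this review, and a journal article condenses a fuller protocol. A reader might infer that the trial collects no feeding status in the first week. The text supports only that none is listed. That part of the objection stands, and the fix is conditional for this reason. The complications example is weak evidence of an incomplete list, however, because the diary covers complications in both arms, and no stated outcome calls for feeding status at week 1.

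Second, a reader might infer that carry-forward has only day 1 to work from, or cannot operate at all at 1 month. Neither follows. A diary kept up to the point of stopping and then handed in gives a later observation, and a woman who has stopped breastfeeding may still see her obstetrician. The rule also works for a woman who has already stopped on day 1. The gap is confined to women who stop after day 1 and whose diary is never recovered.

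Third, the comparison with and without imputed data does not share the gap in full: the analysis without imputation does not use carry-forward at all. The comparison can show that imputation matters, but it cannot recover what these women were doing when last reached.

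**Conclusion.** The concern holds in this limited form. For women lost before the 1-month visit without a recovered diary, the text lists nothing on feeding after day 1, and carry-forward will rarely apply to those who stopped in between. Random replacement is the apparent fallback, but the plan does not fix it for these women, so they may instead be left missing.

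The size is uncertain. A reader might conclude that half of each arm will lack the primary outcome, but the protocol does not say when its 50% attrition occurs and follow-up runs to 6 months. Up to 25 per arm is a ceiling, with 15 or 20 at 30% or 40%. The number the added questions would recover rests on the assumed s and excludes women lost before the calls. The twofold spread in the estimate rests on the planning rates holding among observed women and on equal loss in both arms.

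The change is worth making because the missingness concerns the primary outcome, is plausibly related to it, and can be reduced through calls that already take place.

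**What to change.** 1. **Data collection.** Unless Fig. 1 already schedules them, add to the day-3 and day-7 calls, in both arms, the day-1 items: "exclusive breastfeeding (yes/no), use of artificial milk (number of feeds in 24 h, justification"). Also ask whether breastfeeding has stopped and on what date.
2. **Statistical methods.** Name these calls and any recovered diary as the sources for carrying forward to 1 month. State which imputation applies to a woman with no feeding observation after day 1.

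The cost is one or two more questions in calls already scheduled for every participant, a line on the data collection form and a minor amendment. The calls become slightly longer. The change does nothing for women who cannot be reached on day 3 or day 7, nor for those who stop after day 7 and are then lost.

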## Background

Breastfeeding confers several health benefits to infants and their mothers, including protection from infectious and chronic diseases, improved child cognition, development, and intelligence, and decreased risks of maternal depression and malignancies [1–5]. As such, breastfeeding is recommended as the exclusive nutrition for the first 6 months of the infant’s life, with continuation until 2 years complemented with solid foods [6–8]. However, women with inverted nipples often have difficulties in maintaining breastfeeding due to improper infant latching that my cause insufficient milk extraction and poor infant satiety, thus leading to early termination of breastfeeding. Congenital inversion of the nipple, the most common nipple deformity, is due to early developmental arrest [9], with an estimated prevalence of about 10% [10]. However, nipple inversion can also be acquired secondary to mastitis, macromastia, carcinoma, or breast reduction, or can be associated with congenital syndromes such as Robinow and MR/MCA syndromes [11]. Han and Hong categorized the severity of inverted nipple into three grades. In grade 1, the nipple is easily pulled out manually, maintains good projection, and has minimal fibrosis. Grade 2 includes the majority of inverted nipple cases in which the affected nipple can be pulled out manually but fails to maintain projection and has moderate fibrosis beneath it. Grade 3 constitutes the rarest type of inverted nipples, which cannot be pulled out manually due to severe fibrosis [12].

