The main treatment of inverted nipples is corrective surgery with sectioning of the lactiferous ducts. However, surgery is reserved for the severe grades such as invaginated nipples that are difficult to extract manually (grade 3), and it is not indicated for mild umbilicated nipples that can be momentarily extracted from their inverted positions (grades 1 and 2) [12]. Several non-surgical interventions have been used to extract inverted nipples. Hoffman exercises and the use of Woolwich breast shields, which were routinely recommended, have been shown to be of limited success [13]. The Niplette™ (Philips Avent, Andover, MA, USA) is another simple device that uses gentle negative suction to stretch the lactiferous ducts and extract the nipple with a success rate close to 80% [14]. It consists of a nipple cover, valve, and syringe and is operator dependent with one Niplette needed for each breast [14]. A more recent intervention was described by Chakrabarti and Basu in which a rubber band was put around the nipple base using a syringe applicator with a success rate of 62% [15]. However, this method carries with it certain risks, such as nipple injury, infection, or slipping of the band into the infant’s mouth [15]. The simplest, least expensive, most readily available, and most effective method to extract nipples has been reported in a case series by Kesaree et al. [16]. In this method, women with inverted nipples are trained to use an inverted syringe and apply gentle negative pressure around the nipple to evert it. The procedure can be repeated before each breastfeed as long as required. Of the eight women reported by Kesaree et al., seven (87.5%) infants succeeded in latching within 2 to 7 days, and six (75%) were exclusively breastfeeding at 6 weeks [16]. The main advantage of the inverted syringe over the Nipplette™ and the rubber and syringe technique is the fact that syringes are readily available in all countries, inexpensive, safe, and simple to use. To our knowledge, breastfeeding success with the use of the inverted syringe has not been previously investigated in a clinical trial. In this study, we aim to conduct the first randomized controlled trial to investigate whether the use of the inverted syringe in healthy term pregnant women with inverted nipples improves breastfeeding initiation and continuation rates, as compared to standard care.

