#### Intervention group

We will train the participants allocated to the experimental group on the use of the inverted syringe before each breastfeed as of the first postpartum day. We will also provide them with documentation on the daily use of the syringe, adverse events, breastfeeding-associated complications, use of artificial devices to correct the inverted nipple, the number of artificial milk feeds given to the newborn with their justification in a diary. The research assistant will send weekly reminders to the participants in the experimental group to use the syringe technique before each breastfeed using e-mail, telephone messages, or communication through social media. Syringe use will continue for as long as needed by the mother.

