#### Secondary outcome measures

Secondary outcomes include differences between the two groups in the rates of nipple eversion at 1 month, successful latching of the infant on mother’s breast at 1 month, exclusive breastfeeding at 3 and 6 months, mixed feeding at 1, 3, and 6 months, breastfeeding-associated complications such as sore nipple, mastitis, pain, bleeding, and breast engorgement at 1 week, 1, 3, and 6 months postpartum. Other secondary outcomes are maternal satisfaction with breastfeeding assessed at 1 week postpartum using the validated Maternal Breastfeeding Evaluation Scale [18, 19], and maternal quality of life assessed at 1 month using the validated Postpartum Quality of Life instrument [20] (Fig. 1).

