### Data management and quality assurance

The research assistant will be trained on how to approach eligible women, and how and when to contact them for follow up and data collection. Training entails familiarizing her with all the necessary documentation, including enrollment and consent forms, and consenting in accordance with the ethical principles of the Belmont Report. Demonstration and training on the use of the syringe will also be performed.

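### Nipple eversion at 1 month, a secondary outcome, is judged by a research assistant who knows the allocation, and a difference may partly reflect recent suction or assessor expectation

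*Protocol article*

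**What the plan says.** Secondary outcome measures lists "differences between the two groups in the rates of nipple eversion at 1 month". Data collection names the assessor: "The eversion of the nipple will also be assessed by the research assistant during this visit". The visit is placed by the sentence that begins "The diary will be collected at 30 and 40 days during the", which refers to the woman's postpartum obstetric appointment. The article gives no other timing for the inspection.

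The same role has different contact with the two arms. Under Intervention group: "The research assistant will send weekly reminders to the participants in the experimental group to use the syringe technique before each breastfeed". Under Control group: "The research assistant will send weekly reminders to the participants in the control group", and those messages concern the diary only. Data management and quality assurance describes one role, in the singular: "The research assistant will be trained on how to approach eligible women, and how and when to contact them for follow up and data collection". That training also covers use of the syringe. No separate assessor is named.

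On blinding, Statistical methods and Ethics approval describe the analysis and the analyst as blinded. The Discussion says that the open-label design may raise the risks of performance and detection bias, and that participants would be hard to blind.

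On the condition itself, Background says surgery is not indicated for "mild umbilicated nipples that can be momentarily extracted from their inverted positions (grades 1 and 2"), and states: "In grade 1, the nipple is easily pulled out manually, maintains good projection, and has minimal fibrosis". It adds that grade 2, the majority of cases, can be pulled out by hand but does not stay out. Under Intervention group, the syringe is used before each feed with no fixed end date.

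**The concern.** Eversion is what the device acts on directly, and it is judged by inspection. Two features could move the result towards the syringe without any lasting change in the nipple.

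- **Assessor expectation.** The person judging eversion has spent weeks prompting one arm, and not the other, to use the technique.
- **Recent suction.** If a nipple can be drawn out for a time, what is seen depends partly on how recently that was done. The intervention makes recent drawing-out more likely in one arm.

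At stake is what the eversion result can mean. The abstract's Discussion paragraph says positive findings would support an intervention to treat inverted nipples. As measured, a difference would not separate an everted nipple at rest from one lately drawn out for a feed.

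**Working it through.** **The plan's own figure.** The only calculation in the article is for the primary outcome (40% v 5%, 90% power, 5% type I error). With unpooled variance and a two-sided test:

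n = [0.40×0.60 + 0.05×0.95] × [(1.960 + 1.282)/0.35]² = 24.66, rounded up to 25 per group. Then 25/(1 − 0.50) = 50 per group, 100 in total.

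This reproduces the stated figures. The eversion point does not depend on it; it only supplies 25 and 50 per arm as plausible numbers assessed.

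**Does the assessor know the arm?** Three statements, side by side:
1. The research assistant assesses eversion (Data collection).
2. The research assistant reminds experimental women to use the syringe (Intervention group).
3. The research assistant reminds control women about the diary only (Control group).

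With one role described and no other assessor named, the assessor as written knows each woman's arm. The experimental diary, collected at the same visit, also records daily syringe use.

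**Can the state of the nipple be temporary?** Eligible grades can be momentarily drawn out. Grade 1 then holds projection; grade 2 does not. Syringe use may be ongoing at the visit. Recent use can therefore affect what is seen, more for grade 1 than for grade 2.

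**Size, on assumed inputs.** The article gives no eversion rates, so everything below is illustrative.

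*Illustration A.* Let p be true eversion at rest, equal in both arms, and r the share of the remaining women who are scored everted because of recent drawing-out. Then observed rate = p + (1 − p)r. With p = 0.30:
- r = 0.40 (experimental): 0.30 + 0.70×0.40 = 0.58
- r = 0.10 (control): 0.30 + 0.70×0.10 = 0.37, a spurious difference of 21 points
- r = 0.20 (experimental) against 0.10 (control): 0.44 − 0.37 = 7 points

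These values count every recently drawn-out nipple as everted. If only a share h still projects at inspection, the difference becomes h(1 − p)(r₁ − r₀), where r₁ and r₀ are the experimental and control shares. It shrinks in proportion to h and vanishes at h = 0.

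*Illustration B.* Let f be the net share of non-everted experimental women scored everted, from either cause, with none among controls. The scored experimental rate is q = p + (1 − p)f, the difference is d = q − p, and p̄ is the mean of q and p. The chance of a significant result favouring the syringe (nominal 2.5%) is approximately

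Φ{[d − 1.96√(2p̄(1 − p̄)/n)] / √([q(1 − q) + p(1 − p)]/n)}.

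Example with p = 0.20, f = 0.10, n = 25: q = 0.28, d = 0.08, p̄ = 0.24. This gives (0.08 − 1.96×0.1208)/0.1203 = −1.303, and Φ = 0.096.

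| p | f | Scored everted, syringe v control | Chance, 25 per arm | Chance, 50 per arm |
|---|---|---|---|---|
| 20% | 10% | 28% v 20% | 10% | 15% |
| 20% | 20% | 36% v 20% | 24% | 43% |
| 20% | 30% | 44% v 20% | 44% | 74% |
| 40% | 10% | 46% v 40% | 6% | 9% |
| 40% | 20% | 52% v 40% | 13% | 22% |
| 40% | 30% | 58% v 40% | 24% | 44% |

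**The case against.** The case on the other side has real force.

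- **The limitation is disclosed.** The Discussion names detection bias, which is bias in outcome assessment. A reader might infer that the authors overlooked it; they did not. What is absent is a safeguard for this outcome.
- **The article is condensed.** Examination at rest and the interval since the last feed could sit in a manual or in the schedule figure, which is not shown. That stands: silence on timing is not an error by itself. The choice of assessor, however, is stated.
- **The mechanism is limited.** A reader might infer that any nipple inspected soon after suction will look everted. Background says otherwise for grade 2, the majority. Control women also feed and may use shields, pumps or the syringe itself, and some experimental women may have stopped by the visit. All of this reduces the asymmetry without showing that it is absent.
- **The form of the outcome is not settled.** A reader might infer a plain yes/no judgement with no grade recorded. The article speaks of eversion rates but does not say that grade goes unrecorded at 1 month.
- **Masking is not simple.** The woman's obstetrician directs care in the control arm and may know the allocation. Asking about last syringe use at the inspection would also reveal the arm. Both points shape the fix.

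**Conclusion.** The point holds as a measurement weakness in one secondary outcome. As written, the assessor knows the allocation, and the protocol's own account of grades 1 and 2 gives a route by which ongoing syringe use could affect what is seen. A difference may therefore partly reflect recent suction or assessor expectation.

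The size cannot be derived from the document. The 7 and 21 points, and the 6% to 74% chances of a false finding, rest wholly on assumed eversion and misclassification rates. They also make no allowance for grade 2 nipples losing projection. That one person both assesses and reminds is read from the singular role description.

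A reader might go further and conclude that an eversion benefit would be spurious, or that the trial's main result is compromised. The documents support neither: bias is possible, not shown, and the primary outcome (exclusive breastfeeding at 1 month) and the sample size are untouched. The change is worth making because it is cheap and clarifies what the eversion result can claim.

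**What to change.** At the 1-month visit:

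1. First record whether each nipple is everted at rest, before any handling, feeding or device use at that visit. Then grade it on the three-grade inversion scale used at entry.
2. Apply the same prespecified minimum interval since the last feed or device use in both arms. If the full protocol already sets one, cite it.
3. Enter the grade before the diary is collected. Have the time since the last feed or device use recorded separately, so that the question does not reveal the arm to the assessor.
4. If someone already on site sends no reminders and is not told the allocation, that person should do the grading. Otherwise keep the research assistant, report the outcome as assessor-unblinded and interpret it accordingly.

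The cost is a few added form entries and a set order of steps at a visit that already takes place; a different grader would also need brief training on the scale. The downside is that some women will have fed or used a device shortly before and must wait or be flagged.
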